# Safety, effectiveness, and economic evaluation of an herbal medicine, Ukgansangajinpibanha granule, in children with autism spectrum disorder: a study protocol for a prospective, multicenter, randomized, double-blinded, placebo-controlled, parallel-group clinical trial

**DOI:** 10.1186/s13063-019-3537-7

**Published:** 2019-07-15

**Keywords:** Herbal medicine, Acupuncture, Autism spectrum disorder, Randomized controlled trial, Ukgansangajinpibanha

## Abstract

**Background:**

Autism spectrum disorder (ASD) is characterized by continuous impairment in communication and social interaction and by limited and repetitive behaviors, interests, or activities. Behavioral, educational, and pharmaceutical interventions have been shown to reduce behavioral disabilities, improve verbal/non-verbal communication, and help patients acquire self-reliance skills. However, there has been a lack of systematic verification and consensus regarding the treatment of the core symptoms of ASD because of its unclear etiology. Ukgansangajinpibanha (UGSJB), a legitimately prescribed herbal medicine for nervousness, insomnia, night crying, and malnutrition in South Korea and Japan, has been used for angry, sensitive, nervous, and unsettled children with ASD.

**Methods/design:**

This trial is a prospective, multicenter, randomized, double-blinded, placebo-controlled, parallel-group, clinical trial. The 4- to 6-year-old children with ASD will be randomly assigned to following groups:A UGSJB granule with acupuncture, twice daily (n = 120)A placebo group with acupuncture, twice daily (n = 120).

The following outcome measures will be used: behavior by the Childhood Autism Rating Scale, Autism Behavior Checklist, and Aberrant Behavior Checklist; social maturity by the Social Maturity Scale; quality of life by the Child Health Questionnaire and EuroQoL Five-dimension Five-level Youth; and parental stress by the Parenting Stress Index at baseline and at 6, 12, and 24 weeks after the beginning of treatment.

In addition, to evaluate safety, we will investigate the adverse reactions that may be caused by UGSJB granule. Finally, we will make an economic evaluation of UGSJB for the treatment of ASD.

**Discussion:**

We prepared a well-designed clinical trial to investigate the safety and effectiveness of UGSJB on ASD symptoms compared with placebo treatment. The results from this study will provide clinical evidence on the safety, effectiveness, and economic value of UGSJB combined with acupuncture in children with ASD.

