Ukgansangajinpibanha (UGSJB), which is made from Ukgansan by adding Citri Pericarpium and Pinelliae Rhizoma, has been more often used in children with indigestion compared with Ukgansan. Similar to Ukgansan, it has been administered to angry, sensitive, nervous, and unsettled children with ASD [13]. Unlike Ukgansan, UGSJB is legitimately prescribed as an herbal formula granule for nervousness, insomnia, night crying, and malnutrition in South Korea and Japan [14]. Interestingly, children with ASD tend to experience more gastrointestinal symptoms than children without ASD [15]. Therefore, we prepared a well-designed clinical trial to investigate the safety and effectiveness of UGSJB on ASD symptoms compared with placebo treatment. The results of this trial will provide evidence of whether UGSJB is safe and effective for the treatment of ASD in children.

Acupuncture, a treatment supported by the National Health Service in South Korea, will be provided to every participant for an economic evaluation. Acupuncture has weak evidence of benefits but is a safe and effective treatment for ASD [16]. Frequently used acupoint for treating ASD sympstoms are EX-HN1, GV17, PC6, LR3, KI3, HT7, LU9, GV20, GV24, GV24.5, GB13, GB19, KI4, LR4, ST36, SP3, and SP6 [17]. We decided to use EX-HN1, GV20, and GV24 for acupuncture treatment of ASD in children because these acupoints have been frequently used in RCTs on ASD [18], and scalp acupuncture decreased scores of Childhood Autism Rating Scale (CARS) and Autism Behavior Checklist (ABC^1^) of children with ASD [19]. UGSJB in combination with acupuncture will be evaluated from an economic perspective.

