*Cnidium officinale* Makino (Umbelliferae)	Dried rhizome	KP	0.5
*Uncaria sinensis* Havil. (Rubiaceae)	Dried ramulus	KHP	0.5
*Bupleurum falcatum* Linné (Umbelliferae)	Dried root	KP	0.34
*Glycyrrhiza glabra* L. (Leguminosae; licorice)	Dried root and rhizome	KP	0.25

*Abbreviations*: *KHP* Korean Herbal Pharmacopoeia, *KP* Korean Pharmacopoeia.

Scalp acupuncture will be performed in all participants by using six fixed points at GV20 (Bai Hui), GV24 (Shen Ting), and EX-HN1 (Si Shen Cong) in a total of 24 sessions for 12 weeks. We considered participants who attended 75% or more (≥18 of 24) of the acupuncture sessions to have completed a full course of treatment. A 0.25 × 40 mm disposable sterilized stainless-steel needle will be used. GV20 and GV24 were inserted backward and EX-HN1 was inserted outward. After insertion of the needle (10–15 mm of depth), it will be stirred by hand until de qi sensation. The inserted needle will remain for 30 min with available manual stimulation. If the child pulls out the needles during the procedure, other needles will be inserted. Acupuncture will be performed by Korean medicine doctors with 3 years of acupuncture training and more than 1 year of clinical experience. If the participant strongly complains of discomfort, the practitioner will stop the acupuncture procedure.

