## Discussion

Herbal medicines which have been shown to be effective for ASD in RCTs include Jiawei Wendan decoction, modified Yinhuo decoction, and supplemented Lizhong decoction [34]. Modified Yinhuo decoction and supplemented Lizhong decoction improve CARS and the total effective rate, and Jiawei Wendan decoction improves the total effective rate. However, there were some methodological limitations. For example, the number of participants in each group was less than 30 and all studies were unblinded. Our study will be the first prospective, multicenter, randomized, double-blinded, placebo-controlled, parallel-group clinical trial assessing the safety, effectiveness, and economics of an herbal medicine combined to acupuncture in the treatment of ASD.

ASD is generally diagnosed around 4 years of age [35], and the UGSJB dose administered to 4- to 6-year-old children ages is half that of adults. Moreover, the golden time for ASD treatment is known to be between the ages of 2 and 6 [36]. We decided to enroll 4- to 6-year-old children with ASD for the best effectiveness using a single capacity of UGSJB. The treatment period was set to be 3 months, following the previously effective herbal treatment RCTs. Acupuncture, a treatment supported by the National Health Service in South Korea, will be implemented in all groups for economic comparison. The behavior of children with ASD will be evaluated by CARS, ABC^1^, and ABC^2^. Social maturity will be assessed by SMS. Quality of life will be evaluated by CHQ-PF28 and EQ-5D-Y proxy 1. Stress of parents of children with ASD will be assessed by K-PSI-SF. The safety of USGJB will be investigated on the basis of voluntarily reported AEs, and the economic evaluation of USGJB will be analyzed by CEA, CUA, and CBA.

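### Acupuncture is common to both arms, so the trial can give the economic value of UGSJB added to acupuncture, not of acupuncture or of the combination

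*Protocol article*

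**What the plan says.** **Design.** The Interventions section randomises children to UGSJB or placebo granules. It then states: "Scalp acupuncture will be performed in all participants by using six fixed points", for 24 sessions over 12 weeks. The abstract likewise lists acupuncture in both arms. No arm goes without acupuncture, and there is no sham acupuncture arm.

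**Passages that name the combination, or give acupuncture an economic purpose.**
- The closing sentence of the abstract promises "clinical evidence on the safety, effectiveness, and economic value of UGSJB combined with acupuncture in children with ASD".
- The Background says acupuncture "will be provided to every participant for an economic evaluation" and that "UGSJB in combination with acupuncture will be evaluated from an economic perspective".
- The Discussion repeats that acupuncture "will be implemented in all groups for economic comparison". It also presents the trial as one of herbal medicine combined with acupuncture.

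**Passages that name UGSJB, or UGSJB as an add-on.**
- Study design gives the aim as the effectiveness of UGSJB.
- The sentence of the abstract just before its closing one sets UGSJB against placebo.
- For safety and effectiveness, the Background names UGSJB alone, against placebo.
- The Discussion, in its paragraph on planning concerns, describes testing the herbal medicine as an addition to acupuncture with existing treatment kept constant.

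**Economic analysis.** The Economic evaluation section reports cost-effectiveness as an average ratio (ACER) or an incremental ratio (ICER), and cost-utility as an average ratio (ACUR) only. The option with the lowest average ratio is to be chosen. An ICER under an unspecified level counts as cost-effective.

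**The concern.** A component given identically to both arms cannot be the subject of a comparison between them. Giving acupuncture to everyone makes it part of the setting in which UGSJB is tested. It does not make acupuncture, or the package of UGSJB plus acupuncture, something whose value is estimated.

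At stake is what the trial may conclude, above all economically. A ratio calculated for the UGSJB arm alone looks like the value of the package, but nothing in the randomisation supports it. A payer could then credit acupuncture, or the package against usual care, with a value that was not tested.

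**Working it through.** **1. The plan's own figure.** Inputs from Sample size calculation: CARS changes of −7.9 (SD 5.42) and −4.6 (SD 5.53), two-sided 5% level, 80% power, 1:1 allocation, 25% withdrawal.
- Difference: 7.9 − 4.6 = 3.3.
- Pooled SD: √[(5.42² + 5.53²)/2] = 5.475.
- Normal approximation: n = 2 × (1.960 + 0.842)² × 5.475² / 3.3² = 43.2, so 44 per group.
- Two-sample t test: 44.2, so 45 per group.
- Allowing for withdrawal: 45 / 0.75 = 60 per group, 120 in total.

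The stated numbers reproduce. They power one contrast, UGSJB against placebo. (The abstract's 120 per group conflicts with 60 per group. That is a separate matter.)

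**2. What the two arms identify.** Write the mean improvement in each arm as a sum:
- b = natural course and existing treatments
- p = placebo response
- a = acupuncture
- u = UGSJB
- i = any interaction between UGSJB and acupuncture

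UGSJB arm: E1 = b + p + a + u + i.

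Placebo arm: E0 = b + p + a.

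Difference: E1 − E0 = u + i.

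This is the effect of UGSJB in children who are also receiving acupuncture. The effect of the combination against care without acupuncture would contain a + u + i, and a cannot be separated from b and p with these two arms. The same reasoning applies to adverse events.

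**3. Costs.** Let C1 and C0 be the mean costs per arm. The cost of acupuncture is in both and drops out of C1 − C0 if the arms attend equally often. Attendance may vary, since 18 of 24 sessions counts as a full course. A difference in attendance would then enter C1 − C0, but as part of the comparison of UGSJB with placebo, not as a valuation of acupuncture.

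**4. Incremental against average ratios.**
- ICER = (C1 − C0)/(E1 − E0). Numerator and denominator are both randomised contrasts.
- ACER or ACUR for the UGSJB arm = C1/E1. This carries the full cost of acupuncture above the line and b + p + a below it.

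With E0 and E1 − E0 both positive, choosing the lower average ratio means choosing UGSJB when

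(C0 + ΔC)/(E0 + ΔE) < C0/E0, that is, when ΔC/ΔE < C0/E0.

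The rule thus compares the ICER with the placebo arm's own average ratio. Acupuncture cost and background change set that threshold, although neither is evaluated. Average ratios do not supply the missing comparator.

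**The case against.** The strongest reply is that the article asks the right question in several places, and that UGSJB combined with acupuncture can simply mean UGSJB given on top of acupuncture and tested against placebo given on top of acupuncture. Nowhere does it say that the effect of acupuncture, or of the combination against usual care, will be estimated. The fuller economic plan may also sit in the unpublished protocol.

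Much of this stands, and it keeps the point small. The charitable reading does not explain why a treatment common to both arms is said to serve an economic comparison. Nor does it fit the Background sentence that makes the combination the object of the economic evaluation. The rule on average ratios is printed in the article and is not merely left out of it.

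Some stronger readings are tempting and are not supported:
- **That 4.6 of 7.9 CARS points, or 58%, of the change in the UGSJB arm is unattributable.** The two figures come from a cited trial of herbal medicine plus behavioural education against behavioural education alone. Acupuncture is in neither arm as described, so they say nothing about how change in this trial would divide.
- **That the plan will report change within the UGSJB arm as the benefit of the combination.** The sample size hypothesis is a difference between groups, Statistical analysis tests between groups, and tests within groups are labelled secondary.
- **That acupuncture cancels completely.** Its separate effect does, but an interaction with UGSJB stays in the contrast. Cost cancels only with equal attendance.
- **That the Background overclaims on safety and effectiveness.** It names UGSJB alone for these. Only its economic wording reaches the combination.

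**Conclusion.** The point holds in a narrow form and is minor. The trial can estimate the effect, safety and incremental cost-effectiveness of UGSJB added to acupuncture and existing treatment. The abstract's closing sentence, together with the economic statements in the Background and the Discussion, gives acupuncture and the combination a purpose that two arms sharing acupuncture cannot serve. Those statements also disagree with the Study design section and with the add-on wording in the Discussion.

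No numerical size can be put on this from the article. The missing comparator follows from the allocation alone and depends on no assumed effect. The cancelling of acupuncture cost does assume equal attendance. A reader might infer that the trial itself is flawed. The documents do not support that: the comparison of UGSJB with placebo is valid on its stated background, and 45 evaluable and 60 enrolled per group are unaffected.

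**What to change.** - In the abstract conclusion and the economic objective, use the add-on wording that the Discussion already contains: UGSJB against placebo, each added to scalp acupuncture and existing treatment.
- Replace the economic reason for acupuncture in the Background and Discussion with a statement that it is common background whose own effect and value are not evaluated.
- In Economic evaluation, rest the conclusion on the incremental comparison between arms, and add an incremental cost-utility ratio beside the ICER. Average ratios per arm may be shown as description, but neither they nor change within an arm should decide the conclusion.

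The cost is some rewording, one added incremental ratio from data already planned, and a narrower claim. Visits, treatment, randomisation and sample size stay as they are. A claim for the value of the combination itself would need an arm without acupuncture, which is a different trial.

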**Trial registration:**

Clinical Research Information Service: KCT0003007 (registered on April 5, 2018)

**Electronic supplementary material:**

The online version of this article (10.1186/s13063-019-3537-7) contains supplementary material, which is available to authorized users.

## Background

Autism spectrum disorder (ASD) is characterized by continuous impairment in communication and social interaction (diagnostic criteria A) and by limited and repetitive behaviors, interests, or activities (diagnostic criteria B). These symptoms appear early in childhood and negatively affect daily functions (diagnostic criteria C and D) according to the *Diagnostic and Statistical Manual of Mental Disorders* (5th edition) [1]. The prevalence rate of ASD is four times higher for boys than for girls and has increased since the 1970s, especially from the late 1990s [2]. The prevalences of ASD are 2–20 per 1000 people in recent studies in Europe, Asia, and the US and 7.6 per 1000 people according to a global systematic review in 2010 [3]. Causes of ASD are unclear, but gene abnormalities altering brain development, brain damage at birth, and maternal effects during pregnancy have been suggested.

General therapeutic goals of ASD are to reduce behavioral disabilities, improve verbal/non-verbal communication, and provide patients with self-reliance skills. Non-pharmaceutical treatments aim to improve ASD symptoms through individualized behavioral and educational interventions, including behavioral and developmental programs, cognitive behavioral therapies, occupational therapies, sensory integration therapies, sleep management, and communication facilitation [4]. Pharmaceutical treatments, including risperidone, aripiprazole, methylphenidate, and haloperidol, are generally used as adjunctive therapies to reduce the accompanying symptoms such as aggression, anxiety, depression, hyperactivity, stereotypic and self-harm behavior, and insomnia rather than the core symptoms of ASD [5]. However, there has been a lack of systematic verification and consensus regarding the treatment of the core symptoms of ASD because of its unclear etiology.

ASD children can be hurt psychologically by passively accepting many criticisms in life because of their unusual behavior. In traditional Chinese medicine (TCM) theory, the persistent emotional stimulus affects the function of liver free coursing and causes stagnation of liver qi. Dysfunction of liver free coursing is often found in the early stages of ASD, which are characterized by mental depression and apathetic expression. Depressed liver qi transforms into fire, which is characterized by agitation and anger, red face and eyes, and constipation and yellow urine. Prolonged stagnation of liver qi causes growth retardation, introverted behavior, and an autistic state. ASD children disregard other people, fail to look at each other, and avoid one’s eyes. Those are also dysfunctions of liver free coursing because, from a TCM perspective, liver function is reflected in the activity of the eyes.

Ukgansan (抑肝散 in Chinese, Yokukansan in Japanese), an herbal medicine consisting of Atractylodis Rhizoma White, Poria, Angelicae Gigantis Radix, Cnidii Rhizoma, Uncariae Ramulus et Uncus, Bupleuri Radix, and Glycyrrhizae Radix, was made by Xue Ji in 1556 for treating children’s liver dysfunction such as contracture, convulsion, and epilepsy [6]. It inhibits hypersensitivity and hyperactivity of ASD through anti-inflammatory actions, neurogenesis, and serotonin and glutamate upregulation [7]. In a neurodevelopmental disorder model, Ukgansan decreases grooming in the open field [8]. Ukgansan and Gyejitang (桂枝湯) prevent behavioral abnormalities and improve neuroplasticity signaling in a social isolation model in mice [9]. In a 12-year-old boy with ASD, Ukgansan improved irritability, which had not been successfully treated with anti-psychotic drugs [10]. Ukgansan was administered to 20 children (6–17 years old) with pervasive developmental disorder (PDD) for 12 weeks; as a result, irritability/agitation and hyperactivity/non-compliance subscale scores of the Aberrant Behavior Checklist (ABC^2^) were significantly improved [11]. In another study, Ukgansan was administered to 40 patients (8–40 years old) with PDD-not otherwise specified or Asperger’s syndrome for 12 weeks, and ABC^2^ irritability subscale scores were also significantly improved [12]. However, the effectiveness of Ukgansan or similar prescriptions has not yet been investigated in randomized controlled trials (RCTs).

Ukgansangajinpibanha (UGSJB), which is made from Ukgansan by adding Citri Pericarpium and Pinelliae Rhizoma, has been more often used in children with indigestion compared with Ukgansan. Similar to Ukgansan, it has been administered to angry, sensitive, nervous, and unsettled children with ASD [13]. Unlike Ukgansan, UGSJB is legitimately prescribed as an herbal formula granule for nervousness, insomnia, night crying, and malnutrition in South Korea and Japan [14]. Interestingly, children with ASD tend to experience more gastrointestinal symptoms than children without ASD [15]. Therefore, we prepared a well-designed clinical trial to investigate the safety and effectiveness of UGSJB on ASD symptoms compared with placebo treatment. The results of this trial will provide evidence of whether UGSJB is safe and effective for the treatment of ASD in children.

Acupuncture, a treatment supported by the National Health Service in South Korea, will be provided to every participant for an economic evaluation. Acupuncture has weak evidence of benefits but is a safe and effective treatment for ASD [16]. Frequently used acupoint for treating ASD sympstoms are EX-HN1, GV17, PC6, LR3, KI3, HT7, LU9, GV20, GV24, GV24.5, GB13, GB19, KI4, LR4, ST36, SP3, and SP6 [17]. We decided to use EX-HN1, GV20, and GV24 for acupuncture treatment of ASD in children because these acupoints have been frequently used in RCTs on ASD [18], and scalp acupuncture decreased scores of Childhood Autism Rating Scale (CARS) and Autism Behavior Checklist (ABC^1^) of children with ASD [19]. UGSJB in combination with acupuncture will be evaluated from an economic perspective.

## Methods/design

### Study design

This study is a prospective, multicenter, randomized, double-blinded, placebo-controlled, parallel-group, clinical trial. The aim of the clinical trial is to evaluate the effectiveness of UGSJB in 4- to 6-year-old children with ASD, including childhood autism, Asperger’s syndrome, and PDD-not otherwise specified, diagnosed according to the Korean Standard Classification of Diseases (7th edition) by any physician who has not participated in this study. The study protocol conforms to the Standard Protocol Items: Recommendations for Interventional Trials (Additional file 1), Consolidated Standards of Reporting Trials extension for reporting herbal medicines, and Standards for Reporting Interventions in Clinical Trials of Acupuncture. The trial will be performed in accordance with the Declaration of Helsinki and the Ethical Guideline for Clinical Research, and the trial protocol has been approved by the Ministry of Food and Drug Safety (#31635) and the institutional review board (IRB) at Kyung Hee University Korean Medicine Hospital at Gangdong (KHNMCOH 2017–08-008) and Kyung Hee University Korean Medicine Hospital (KOMCIRB 2017–10-041). The trial protocol has been registered with Clinical Research Information Service (KCT0003007) (Appendix: Table 2).

### Study participants

One hundred twenty children will be recruited from two hospitals (Kyung Hee University Hospital at Gangdong and Kyung Hee University Medical Center, Republic of Korea) through online and offline recruitment notices, including posters and webpages. Those two hospitals have recruited participants in more than 20 clinical trials that eight studies were completed and 19 studies are recruiting in Kyung Hee University Hospital at Gangdong, and 41 studies were completed and 52 studies are recruiting in Kyung Hee University Medical Center. The participants’ guardians will be provided with research information, such as objectives, procedures, and potential benefits and harms, through standardized interviews. Informed consent will be obtained from children’s guardians prior to the screening process. The participants will be allowed to withdraw from the study at any time. The research procedure will be carried out as shown in Figs. 1 and 2. All participants will undergo a 12-week treatment and 12-week follow-up. After the screening session, children will be scheduled for 24 treatment visits (twice a week) and one follow-up visit (12 weeks after last treatment). Guardians will be sent text messages as reminders of the scheduled visits.

